### Participant recruitment and retention

We plan to enroll 200 participants. Patients are identified through chart reviews, tumor boards, and direct referrals from oncology clinicians. With the clinician’s permission, a research coordinator contacts the patient by phone to explain the study and screen for eligibility. Written informed consent is obtained electronically via the OHSU electronic data management system (REDCap) before or at the first study visit. For patients we cannot contact prior to their first chemotherapy infusion, or who express that they are too overwhelmed for a research visit at their first infusion, we offer to delay study enrollment until the second chemotherapy cycle. Patients are not enrolled after their second chemotherapy cycle because important information about early changes in symptoms and function can no longer be obtained.

We use several strategies to retain participants in the study. One research assistant is assigned to each participant throughout the study to establish a trusting relationship between each participant and a research team member. We minimize participant burden by using home-based data collection (online surveys and passive monitoring devices) and by conducting testing visits in the clinic just prior to regularly scheduled oncology appointments. If participants do not have a scheduled post-treatment clinic visit within the desired time frame, they are asked to schedule a separate research visit at the Knight Cancer Institute. Participants are remunerated for each study visit ($25 for research visits that coincide with clinic visits or $50 for separate post-treatment research visits). Travel compensation is provided for participants who live > 30 miles from OHSU to attend separate post-treatment research visits.

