#### Specific analysis plan

The analysis will proceed in a series of stages.

*Hypothesis 1.1:Worsening neuropathy symptoms will be associated with concomitant worsening in functioning. *

The change over time in each symptom and functioning outcome will be modeled using a mixed-effects modeling framework implemented in the lme4 statistical package for R. The fixed and random effects structure and the shape of change across time (e.g., linear versus nonlinear) will be determined through likelihood ratio model testing and information criteria. Intercepts (initial status) and growth estimates (e.g., linear and/or quadratic trends) will be estimated for each individual patient for each outcome. All pairs of neuropathy symptom and functioning intercepts and slopes will be correlated to test Hypothesis 1.1*.*

*Hypothesis 1.2. At least two classes of patients with distinct trajectories of change in symptoms and functioning can be identified, and will be associated with significant differences in fall rates.*

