 Standard statistical tests will be used to examine the association between latent class membership and sociodemographic, clinical, and mobility measures depending on level of scale (e.g., Kendall/s tau-b or Kruskal–Wallis tests). Since we will recruit both men and women into the study, we can also address sex as a biologic variable in the context of symptoms, functioning, and falls among cancer survivors**.** Thus, we will be the first to determine if sex associates with specific symptom trajectories that might lead to either gender-specific management approaches or a uniform strategy. Since there is a potentially large number of variables that will be compared we will control for false discovery rates with the Hochberg adjustment [59].

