### Sample size/power calculation

Although simulation methods are available to help estimate sample size for

GMM, this requires known values for all model parameters and is not defensible given the unknowns in this domain. With 2 symptom measures (severity and interference) and 6 function measures in our most complex GMM model, however, our n-to-items ratio meets conservative sample size recommendations for related approaches (20:1) [60] and would require 160 complete cases. To maximize statistical power we will fit parsimonious models after extensive preliminary associative analyses. Regarding class comparisons, assuming 80% power, two-sided α of 0.05, and 2 equal groups, we will be able to detect small-medium sized differences in fall rates and other continuous variables between groups (Cohen’s *d* = 0.40). For categorical variables, we will be able to detect small-medium effects (w = 0.25) for cross-tabulation tables with as many as 4 degrees of freedom. Evaluable data on 200 participants is a feasible number and will allow us to address each aim while accounting for up to ~ 20% attrition.

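### Hypothesis 2.1 pairs a false discovery rate target with the name of a family-wise procedure; followed literally, the predictor screen is stricter than its own target requires

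*Protocol article*

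**What the plan says.** In the Protocol article, Specific analysis plan, Hypothesis 2.1, the search for predictors of trajectory class is a set of separate tests: "Standard statistical tests will be used to examine the association between latent class membership and sociodemographic, clinical, and mobility measures". The reason given for adjusting is "Since there is a potentially large number of variables that will be compared", and the rule is that "we will control for false discovery rates with the Hochberg adjustment", with a citation (reference 59) whose content is not shown. The section gives no number of tests and no FDR level.

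The Sample size/power calculation section states what class comparisons can detect, "assuming 80% power, two-sided α of 0.05, and 2 equal groups": d = 0.40 for continuous variables and, for categorical ones, "w = 0.25) for cross-tabulation tables with as many as 4 degrees of freedom". That statement mentions no multiplicity adjustment.

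**The concern.** Two step-up procedures have similar names. Hochberg's compares the k-th smallest of m p-values with α/(m−k+1) and is built to control the chance of any false rejection in the family. Benjamini-Hochberg compares it with qk/m and is built to control the expected share of false rejections among all rejections. The sentence states the target of the second and gives the name of the first. R, which the article names as analysis software, offers them as separate options, so two analysts following the text could produce different predictor lists.

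This is the only multiplicity rule given for Hypothesis 2.1, and these tests serve the third aim, finding a small predictor set for risk of decline and falls. The two procedures differ noticeably when many variables are screened and several are truly associated, which is the setting the plan describes.

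**Working it through.** **1. The plan's own figure.** For two equal classes, n per class = 2(1.960 + 0.842)²/0.40² = 98.1, so 99. With 100 per class the expected z is 0.40 × √(100/2) = 2.83, and power is Φ(2.83 − 1.96) = 0.807 (0.804 with the t distribution). For w = 0.25 at 4 degrees of freedom and 200 patients, the noncentrality is 200 × 0.25² = 12.5 and power is 0.820. Both stated effects reproduce at 200 patients and unadjusted two-sided α = 0.05.

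**2. How the thresholds differ.** At the same level, the ratio of the Benjamini-Hochberg threshold to Hochberg's is k(m−k+1)/m. Since k(m−k+1) − m = (k−1)(m−k) ≥ 0, the ratio is never below 1, so Benjamini-Hochberg rejects everything that Hochberg rejects. The thresholds coincide at k = 1 and k = m and separate in between:
- m = 20, k = 5: 0.05/16 = 0.0031 against 0.05 × 5/20 = 0.0125, a factor of 4.
- m = 40, k = 10: 0.05/31 = 0.0016 against 0.05 × 10/40 = 0.0125, a factor of 7.75.

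**3. Does Hochberg still control the FDR?** Let V be the number of false rejections and R the number of all rejections. Then V/max(R,1) is at most 1 when V > 0, and 0 otherwise. Taking expectations, FDR ≤ family-wise error rate (FWER). A valid family-wise procedure at 5% therefore holds the FDR at 5%. For Hochberg, validity needs independence or suitable positive dependence.

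**4. What the extra strictness costs.** Taken from the plan: d = 0.40, two equal classes, 200 patients. Assumed: the number of tests, the number of real associations, and 0.05 as the level for both procedures (the article gives 0.05 only as the α of the power statement). Each scenario used 20,000 simulated families of two-sided z-tests. Results for independent tests:

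| Tests (real) | Power, Hochberg | Power, Benjamini-Hochberg | Gap, points | FDR, H / B-H | FWER, H / B-H |
|---|---|---|---|---|---|
| 10 (3) | 0.519 | 0.612 | 9.3 | 0.0176 / 0.0352 | 0.0412 / 0.1016 |
| 20 (5) | 0.434 | 0.577 | 14.3 | 0.0150 / 0.0357 | 0.0427 / 0.1376 |
| 20 (10) | 0.453 | 0.678 | 22.5 | 0.0063 / 0.0250 | 0.0320 / 0.1819 |
| 30 (10) | 0.389 | 0.611 | 22.2 | 0.0090 / 0.0333 | 0.0385 / 0.2143 |
| 40 (10) | 0.355 | 0.565 | 21.0 | 0.0103 / 0.0380 | 0.0412 / 0.2285 |

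Power is the average per real predictor. With a correlation of 0.3 between tests, the gap is 9 to 21 points. With no real association (10 or 20 tests), both procedures had FDR close to 0.05 (0.044 to 0.051, simulation error included).

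**5. Sensitivity to attrition.** The article plans for "will allow us to address each aim while accounting for up to ~ 20% attrition". At 80 per class, power is 0.319 against 0.432 for 20 tests with 5 real, and 0.330 against 0.534 for 20 tests with 10 real. Both levels fall; the gaps remain, at about 11 and 20 points.

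**The case against.** The strongest reply is that no wrong method has been shown. False discovery rate next to the name Hochberg is plausibly shorthand for Benjamini-Hochberg, and reference 59 may settle it. If Benjamini-Hochberg is run, the error rate in the text is correct and only the name is abbreviated. A journal article may also leave the FDR level and the software option to a fuller plan. This stands, and it makes the point an ambiguity and not a demonstrated error. It does not remove the point: the article does not merely omit a detail, it supplies a name that belongs to a different procedure.

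A reader might go further and infer that the named method fails to control the FDR. Step 3 shows that this is wrong, and the simulated FDR under Hochberg stayed at or below 0.05 in every scenario.

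A reader might also infer a defect in Hypothesis 1.1, where "All pairs of neuropathy symptom and functioning intercepts and slopes will be correlated to test Hypothesis 1.1" and no adjustment is mentioned. That text makes no multiplicity claim, so it misstates nothing. Whether to adjust that set of correlations is a design choice that an analysis plan not shown here may cover.

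Finally, the size of the loss rests on inputs the article does not give. That is fair: with few tests or few real associations the gap shrinks, and at 10 tests with 3 real it is about 9 points.

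**Conclusion.** The point holds in a limited form. The stated target and the named procedure do not match. Followed literally, the rule is valid for the FDR but stricter than it needs to be: power per real predictor is about 0.36 to 0.52 under Hochberg, against 0.57 to 0.68 under Benjamini-Hochberg, a loss of about 9 to 23 percentage points. These figures assume 10 to 40 tests with 3 to 10 real, d = 0.40, two equal classes of 100, a 5% level and independent tests. More than two classes, unequal classes or the rank tests the plan mentions would change them, but not the direction, because Benjamini-Hochberg never rejects less at the same level.

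If the sponsor meant Benjamini-Hochberg, there is no loss and only the wording needs repair. The stated detectable effects are not affected, since they use unadjusted α.

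**What to change.** In the Hypothesis 2.1 paragraph, replace the Hochberg wording with: Benjamini-Hochberg procedure, FDR q = 0.05, applied to the Hypothesis 2.1 family of tests. Settle this before latent classes are compared with the candidate predictors, so that the choice cannot follow the results.

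The cost is one line of text and one software argument. The statistical price is a higher chance of at least one false predictor: in the scenarios above with real associations and independent tests, about 0.10 to 0.23 instead of 0.03 to 0.04, with the FDR still below 5%. That suits a screen whose declared target is the FDR. If family-wise control is what the sponsor wants, the sentence should say so and drop the reference to false discovery rates, accepting the lower power.

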### Sample size/power calculation

Although simulation methods are available to help estimate sample size for

GMM, this requires known values for all model parameters and is not defensible given the unknowns in this domain. With 2 symptom measures (severity and interference) and 6 function measures in our most complex GMM model, however, our n-to-items ratio meets conservative sample size recommendations for related approaches (20:1) [60] and would require 160 complete cases. To maximize statistical power we will fit parsimonious models after extensive preliminary associative analyses. Regarding class comparisons, assuming 80% power, two-sided α of 0.05, and 2 equal groups, we will be able to detect small-medium sized differences in fall rates and other continuous variables between groups (Cohen’s *d* = 0.40). For categorical variables, we will be able to detect small-medium effects (w = 0.25) for cross-tabulation tables with as many as 4 degrees of freedom. Evaluable data on 200 participants is a feasible number and will allow us to address each aim while accounting for up to ~ 20% attrition.

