 Each patient's intercept and growth estimates for each measure will be entered into a GMM to identify patient clusters with distinct symptom and function trajectory profiles. For each patient, a probability of belonging to each latent class will be assigned, and the highest membership probability will be used to make a final class assignment. Identification of the best-fitting model will be based on information criteria (e.g., Bayesian Information Criterion), where smaller numbers indicate a better fit, convergence (entropy > 0.80), the proportion of the sample in each latent class (not < 5%), posterior probabilities (mean probability of belonging in “most likely” class near 1.0), and the Lo-Mendell-Rubin adjusted likelihood ratio test (which is used to compare alternative models, e.g., k vs. k-1 classes) [53]. After a good fitting GMM model is found, the resulting latent classes will be described with respect to differences between initial CIPN symptom and functioning profile and change across time. Standard statistics (e.g., t-tests) will then be used to compare fall rates between the observed symptom and function latent classes. We will focus interpretation on effect sizes and 95% CIs. Beyond examining fall rates across the study time course, we will also explore survival models to predict time to first fall. Kaplan Meier models, Mantel-Cox log-rank tests and generalized Wilcoxon-Breslow tests will be used to evaluate differences in the distribution of time to first fall. Multivariate hazard ratios with 95% CIs and Wald χ2 statistics will be calculated from Cox models with Schoenfeld residuals used to test proportional hazards assumptions.

*Hypothesis 2.1. Sociodemographic (e.g., age, sex, comorbidities, body mass index), clinical (e.g., type of chemotherapy, # of chemotherapy cycles and/or cumulative dose of chemotherapy, disease stage, other symptoms), and mobility measures (gait and balance) can be used to predict distinct trajectories of change in neuropathy symptoms and functioning.*

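### The 20:1 sample-size ratio counts 8 measures, but the class model as described takes 16 to 24 indicators, so the claim that 20:1 is met is not supported

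*Protocol article*

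**What the plan says.** The section Sample size/power calculation sets simulation aside, on the ground that too many model parameters are unknown, and relies on a ratio of cases to items. The count is introduced with "With 2 symptom measures (severity and interference) and 6 function measures in our most complex GMM model", and the conclusion drawn is that "our n-to-items ratio meets conservative sample size recommendations for related approaches (20:1) [60] and would require 160 complete cases". The same section then links the 160 to enrolment: "Evaluable data on 200 participants is a feasible number and will allow us to address each aim while accounting for up to ~ 20% attrition".

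The method is described under Statistical analysis. The overview of the modeling strategy sets out two stages: a mixed-effects growth model for each outcome, whose estimates are then passed to a latent class (latent profile) model. The specific analysis plan says of the first stage: "Intercepts (initial status) and growth estimates (e.g., linear and/or quadratic trends) will be estimated for each individual patient for each outcome". Of the second stage, under Hypothesis 1.2, it says: "Each patient's intercept and growth estimates for each measure will be entered into a GMM".

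**The concern.** The sample-size section counts measures. The analysis section enters several derived variables per measure. If an item is a variable entered into the class model, the count of 8 is too low by a factor of two to three, and so is the stated requirement.

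The ratio is the only sample-size argument offered for finding the classes. The other two power statements (d = 0.40 for continuous variables, w = 0.25 for cross-tabulations) concern comparisons between classes once they exist. The fall-rate comparison under Hypothesis 1.2 and the predictor analyses under Hypothesis 2.1 both use the resulting class membership. A reader who is told that a conservative standard is met will place more trust in the class-finding step than the stated argument supports.

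**Working it through.** **Inputs from the protocol article**

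- Measures in the most complex model: 2 + 6 = 8 (Sample size/power calculation).
- Ratio relied on: 20:1 (same section).
- Complete cases stated: 160. Enrolment: 200, with up to about 20% attrition (same section).
- Variables entered at the second stage: an intercept and growth estimates for each measure (Overview of modeling strategy; Hypothesis 1.2).
- Growth terms per measure: linear and/or quadratic, with the shape chosen by likelihood ratio tests and information criteria (Hypothesis 1.1).

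**Step 1. Reproduce the stated figures**

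- Required cases = ratio × items = 20 × 8 = 160.
- Enrolment = 160 / (1 − 0.20) = 200.

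Both match exactly, so the multiplication is sound. The question is the number of items.

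**Step 2. Count the variables that enter the second stage**

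Indicators = measures × (1 intercept + number of growth terms).

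- Linear for all: 8 × 2 = 16.
- Linear plus quadratic for all: 8 × 3 = 24.
- Quadratic for only some measures: 17 to 23.

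**Step 3. Recompute the ratio and the requirement**

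| Count used | Items | 160 cases | 200 cases | Complete cases for 20:1 | Enrolment at 20% attrition |
|---|---|---|---|---|---|
| Measures, as in the protocol | 8 | 20:1 | 25:1 | 160 | 200 |
| Intercept + linear | 16 | 160/16 = 10:1 | 200/16 = 12.5:1 | 20 × 16 = 320 | 320/0.80 = 400 |
| Intercept + linear + quadratic | 24 | 160/24 = 6.7:1 | 200/24 = 8.3:1 | 20 × 24 = 480 | 480/0.80 = 600 |

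Mixed cases (17 to 23 indicators) run from 9.4:1 to 7.0:1 at 160. When each of the 8 measures supplies an intercept and at least one growth term, neither 160 nor 200 cases reaches 20:1.

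**Step 4. Does a lower ratio by itself mean worse classes?**

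This was examined in a small simulation. Its settings are assumptions, not protocol figures: n = 160, two true classes split 30/70, independent normal indicators with common variances, 80 replicates, and one to three classes compared by BIC. The percentages are approximate at that number of replicates.

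- Classes 0.8 SD apart on every indicator: going from 8 to 16 to 24 indicators raised correct assignment from about 86% to 94% to 97%. BIC chose two classes in about 84%, 100% and 100% of runs.
- Same separation, but only 8 indicators informative and the rest noise: correct assignment was about 85% with 16 indicators and 84% with 24. BIC chose two classes in only about 26% and 0% of runs.
- Separation of 1.0 SD on the 8 informative indicators: BIC chose two classes in about 89% (16 indicators) and 56% (24) of runs.

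Extra indicators helped when they carried information and hurt when they did not. Where they hurt, BIC missed the second class; no run selected a spurious third.

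**The case against.** **An item may mean a measure.** The rule is borrowed from related approaches through a citation that is not at hand. If that source counts a measure once, however many terms it contributes, 20:1 survives. This cannot be excluded, and it is why the claim should be called unsupported rather than proven false. But the protocol neither states nor justifies that reading, and the variables its class model receives are intercepts and slopes.

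**Sixteen is not a strict floor.** The random-effects structure is chosen by model fit. A measure with no supported random slope gives every patient the same slope, which cannot act as an indicator. That is fair. Even so, the plan says that growth estimates are made for each patient and each outcome, so 16 is the natural reading and 24 the upper end.

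**The plan has safeguards.** It promises parsimonious models and sets criteria for entropy, minimum class size, posterior probabilities, BIC and the Lo-Mendell-Rubin test. Participants with partial data are retained, so more than 160 may contribute. All of this lowers the stakes. None of it restores 20:1, because the count is given for the most complex model, no reduced indicator set is stated, and even 200 cases fall short.

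**A stronger reading is tempting.** A reader might infer that 160 cases are too few, or that the classes will be unstable and not reproducible. The documents do not support this. They give no class separation, class number or variance structure from which it could be shown, and the simulation above shows that the effect of extra indicators can go either way.

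**Conclusion.** The point holds as a mismatch between the sample-size argument and the model it is meant to justify. Counted on the variables that the analysis section enters, the ratio at 160 complete cases is between 10:1 and 6.7:1, which is one half to one third of the stated 20:1. With all 200 evaluable it is between 12.5:1 and 8.3:1.

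This rests on two assumptions: that an item is an indicator of the second-stage model, and that each of the 8 measures supplies an intercept and at least one growth term. The second follows from the plan's own wording. The first is the natural reading for a latent profile model, but it cannot be checked against the cited source. The conclusion concerns the stated justification only, not whether the enrolment target is adequate.

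**What to change.** In Sample size/power calculation, restate the ratio on the number of second-stage indicators: about 10:1 at 160 complete cases if growth is linear, and about 7:1 if every measure also has a quadratic term. Delete the statement that the 20:1 recommendation is met for the most complex model. This is a change of wording with no effect on recruitment or data collection. The cost is a less favourable ratio on paper.

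Capping the second stage at 8 prespecified indicators would make 20:1 true at 160 cases, for example with intercept and slope of 4 measures (4 × 2 = 8). This is optional and a real trade-off, since it halves the number of measures that define the classes. Using the 8 slopes alone would also fit the cap. But it would take baseline status out of the class definition, although the plan intends to describe the classes by initial profile as well as by change.

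### The stated 80% power at d = 0.40 and w = 0.25 holds for one unadjusted test; the Hypothesis 2.1 comparisons are multiplicity-adjusted, so their power is lower than stated

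*Protocol article*

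**What the plan says.** Under Sample size/power calculation, the article gives detectable effects for comparisons between latent classes. The claim for continuous measures is that "assuming 80% power, two-sided α of 0.05, and 2 equal groups, we will be able to detect small-medium sized differences in fall rates and other" variables of that kind, at d = 0.40. The categorical claim reads: "For categorical variables, we will be able to detect small-medium effects (w = 0.25) for cross-tabulation tables with as many as 4 degrees of freedom". No allowance for multiple testing is mentioned.

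Under Specific analysis plan, two sets of class comparisons are described:

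- **Hypothesis 1.2:** fall rates are compared between classes with standard tests such as the t-test. No adjustment is stated.
- **Hypothesis 2.1:** tests are used to "examine the association between latent class membership and sociodemographic, clinical, and mobility measures depending on level of scale". For these the plan adds: "Since there is a potentially large number of variables that will be compared we will control for false discovery rates with the Hochberg adjustment".

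**The concern.** Apart from fall rates, the class comparisons with a named family of tests are those of Hypothesis 2.1. The continuous and categorical power claims must therefore be meant largely for them. But the power is worked out for one rejection rule (p below 0.05, one test), while those comparisons will be judged by a stricter one (adjusted p over many variables). The two statements stand next to each other and do not match.

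Hypothesis 2.1 serves the aim of finding the simplest set of predictors. A reader who trusts 80% power at d = 0.40 would take a non-significant adjusted result as fair evidence that a predictor of that size is absent. If the true power is materially lower, that inference is too strong.

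**Working it through.** **Inputs from the article.** 200 participants; two equal classes (100 each); two-sided α = 0.05; d = 0.40; w = 0.25 with 4 df; multiplicity adjustment for Hypothesis 2.1.

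**Assumed input.** The number of variables m is not given. The examples under Hypothesis 2.1 name 11 items: age, sex, comorbidities, body mass index, chemotherapy type, cycles, cumulative dose, stage, other symptoms, gait and balance. Counting the seven other symptoms in the Outcome measures section separately gives 10 + 7 = 17, and a few separate gait or balance measures bring it to about 20. I use m = 11 to 20.

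**Step 1: reproduce the plan's figures (one test, α = 0.05).**

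- Two-sample t: noncentrality = d·√(n/2) = 0.40·√50 = 2.83, 198 df, critical value 1.972. Power = 80.4%. The effect detectable at 80% power is d = 0.398.
- Chi-square: noncentrality = N·w² = 200 × 0.0625 = 12.5, 4 df, critical value 9.49. Power = 82.0%. The effect detectable at 80% power is w = 0.244.

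Both match, with almost no margin to absorb an adjustment.

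**Step 2: strictest step of the adjustment (α = 0.05/m).**

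| m | α | Power, d = 0.40 | Power, w = 0.25 | d at 80% | w at 80% |
|---|---|---|---|---|---|
| 1 | 0.05 | 80.4% | 82.0% | 0.398 | 0.244 |
| 11 | 0.0045 | 48.5% | 52.5% | 0.526 | 0.308 |
| 20 | 0.0025 | 41.0% | 45.4% | 0.553 | 0.321 |

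This is a lower bound. Step-up procedures relax the threshold as more variables are truly associated.

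**Step 3: the full step-up procedures.** Sort the p-values. The false discovery rate (Benjamini-Hochberg) rule finds the largest i with p(i) ≤ 0.05·i/m. Hochberg's family-wise rule uses p(i) ≤ 0.05/(m − i + 1). All variables up to that i are declared significant. I simulated independent two-group tests with 100 per class, d = 0.40 for each true association and zero for the rest. Average power per true association, rounded (normal and t statistics differ by up to about 1.5 points):

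| m | True associations | FDR step-up | Hochberg family-wise |
|---|---|---|---|
| 11 | 1 | 50% | 49% |
| 11 | 5 | 67% | 52% |
| 11 | 11 | 78% | 63% |
| 20 | 1 | 43% | 42% |
| 20 | 10 | 67% | 44% |
| 20 | 20 | 78% | 51% |

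The same simulation with 4-df chi-square statistics at w = 0.25 gives about 46% (m = 20, one true) to just under 80% (all true) under FDR, and about 45% to 67% under Hochberg.

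**Step 4: a detectable effect under a middle case.** With m = 11 and about half truly associated, the FDR step-up reaches 80% average power at d of about 0.45.

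**The case against.** The strongest reply has five parts.

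- **The conditions are stated openly.** The article gives α, power and group split, and under them the figures are correct. This stands: there is no slip in the calculation. The fault is that it is applied to comparisons that will be tested differently.
- **The loss may be small.** The plan names false discovery rate control, and its hypothesis expects a combination of predictors, so several true associations are plausible. This stands in part. A reader might infer that power is simply about 50%, and that d of about 0.53 and w of about 0.31 are the right detectable effects. The article does not support that: it fixes neither the number of variables nor the share truly associated. About 50% is the case of 11 variables with one true association, and 0.53 and 0.31 belong to the strictest step. With half true under FDR, power is about 67%.
- **Fall rates are unaffected.** This stands. No adjustment is stated for Hypothesis 1.2, and d = 0.40 is correct there under the plan's own conditions.
- **The harm is conjectural, and the sample size does not rest on d or w.** This stands in part. No text says that non-significant predictors will be discarded, and the enrolment target is argued from an items ratio, feasibility and attrition. So nothing here shows that 200 is too few. The stated power is still a claim that readers will use.
- **Such detail may be left to the full protocol or SAP.** This does not stand. Nothing is missing here; a printed figure disagrees with the analysis described just before it.

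**Conclusion.** The point holds in limited form. The detectable effects are right for one unadjusted test with 200 evaluable patients in two equal classes. For the adjusted Hypothesis 2.1 comparisons, power at d = 0.40 was below 80% in every scenario run. The shortfall is about 2 points if every candidate is truly associated and FDR is used, about 13 points with half true, and 30 points or more with a single true association among 11 to 20. Under Hochberg's family-wise procedure it is about 17 points or more throughout. For w = 0.25 the pattern is similar, except that power is practically at 80% in the all-true FDR case.

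These sizes rest on the assumed 11 to 20 variables, independent tests and equal effects. They also take the plan's best case of 200 evaluable patients ("Evaluable data on 200 participants is a feasible number and will allow us to address each aim while accounting for up to ~ 20% attrition"); losses to follow-up are a separate matter. The wording leaves open which Hochberg-type procedure is meant, but the conclusion does not depend on it.

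**What to change.** In Sample size/power calculation:

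1. Limit d = 0.40 at 80% power and two-sided α = 0.05 to the single fall-rate comparison of Hypothesis 1.2.
2. For Hypothesis 2.1, do one of two things. Either label d = 0.40 and w = 0.25 as per-test figures before adjustment and say that power is lower afterwards. Or restate the detectable effects with the assumed number of variables and share of true associations. For example, with 200 evaluable patients in two equal classes and 11 variables: d about 0.45 if about half are truly associated under an FDR step-up, up to d about 0.53 and w about 0.31 at the strictest step (0.05/11). Use the number of variables actually planned.
3. Add that a non-significant adjusted result for an effect below these sizes is not evidence of no association.

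The cost is a short recalculation and a less favourable stated figure. Enrolment, data collection and analysis are unchanged.

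### The detectable effects for the class comparisons (d = 0.40; w = 0.25 at 4 df) need about 200 and 191 evaluable patients, but enrolment is 200 with up to about 20% attrition

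*Protocol article*

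**What the plan says.** All of the following is in the protocol article.

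- **Enrolment** (Participant recruitment and retention): "We plan to enroll 200 participants".
- **Mixture model** (Sample size/power calculation): eight measures at 20 patients per measure, hence 160 complete cases.
- **Class comparisons** (same section): "assuming 80% power, two-sided α of 0.05, and 2 equal groups, we will be able to detect small-medium sized differences in fall rates" and in other continuous outcomes, with the size given as d = 0.40, and also "small-medium effects (w = 0.25) for cross-tabulation tables with as many as 4 degrees of freedom". No N is attached to either figure.
- **Closing sentence** (same section): "Evaluable data on 200 participants is a feasible number and will allow us to address each aim while accounting for up to ~ 20% attrition".
- **Class sizes** (Specific analysis plan, Hypothesis 1.2): the number and size of the classes come out of model selection. One criterion is "the proportion of the sample in each latent class (not < 5", a floor in per cent of the sample.
- **Withdrawals** (Handling missing data): the growth models are fitted by maximum likelihood on all available data, so a patient with incomplete follow-up is not removed.

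**The concern.** The sample size paragraph justifies 200 patients in two ways: by a patients-per-measure rule for the mixture model and by detectable effects for the class comparisons. The first leaves room for dropout, since 200 less 20% is exactly the 160 required. If the second was computed on all 200, it leaves none, and the closing sentence cannot be true with 200 enrolled: 20% attrition leaves fewer than 200 evaluable.

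The d and w figures are the only power statements for the fall-rate comparison (Hypothesis 1.2) and for the association of predictors with class membership (Hypothesis 2.1). If they hold only with no loss, a non-significant difference in fall rates would be set against a power that the study did not have. Because no N is shown beside the figures, a reader cannot see this without recalculating.

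**Working it through.** **Inputs.** From the sample size section: two-sided α = 0.05, power 80%, two equal groups, d = 0.40, w = 0.25 with up to 4 df, attrition up to about 20%. From the recruitment section: 200 enrolled. Hence the evaluable floor is 200 × 0.80 = 160.

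**Formulas.**
- Continuous outcome: two-sample t-test with noncentrality d·√(n₁n₂/(n₁+n₂)) on n₁+n₂−2 df.
- Categorical outcome: chi-square test with noncentrality N·w².

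**Step 1: reproduce the plan's figures at N = 200.**
- d = 0.40, 100 v 100: noncentrality 0.40 × √50 = 2.83, critical t 1.972, power 80.4%. The smallest d with 80% power is 0.398. The number needed is 100 per class by the t distribution (99 by the normal approximation).
- w = 0.25, 4 df: noncentrality 200 × 0.0625 = 12.5, critical value 9.488, power 82.0%. The smallest N with 80% power is 191.

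The stated figures therefore reproduce at about 200 evaluable patients.

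**Step 2: try N = 160.**
- d = 0.40, 80 v 80: noncentrality 0.40 × √40 = 2.53, critical t 1.975, power 71.0%. Detectable d is 0.446.
- w = 0.25, 4 df: noncentrality 160 × 0.0625 = 10.0, power 71.6%. Detectable w is 0.273.

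A one-sided test at 160 would give a detectable d of 0.395, but the protocol specifies two-sided.

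**Step 3: w by degrees of freedom.**

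| df | N needed for w = 0.25 | Power at N = 160 |
|---|---|---|
| 1 | 126 | 88.5% |
| 2 | 155 | 81.5% |
| 3 | 175 | 76.1% |
| 4 | 191 | 71.6% |

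At 160 the w claim holds for 1 and 2 df and fails for 3 and 4.

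**Step 4: between the floor and full enrolment (equal classes).**

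| Evaluable N | Power, d = 0.40 | Power, w = 0.25, 4 df |
|---|---|---|
| 200 | 80.4% | 82.0% |
| 180 | 76.1% | 77.3% |
| 160 | 71.0% | 71.6% |

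**Step 5: enrolment that would keep the stated figures after 20% loss.** For d: 200/0.80 = 250 (198/0.80 ≈ 248 by the normal approximation). For w at 4 df: 191/0.80 ≈ 239. For the mixture-model rule: 160/0.80 = 200. Only the last matches the planned enrolment.

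**Step 6: unequal classes, as an illustration.** A 20/80 split gives, at N = 200 (40 v 160), power 61.5% for d = 0.40 and detectable d 0.50; at N = 160 (32 v 128), power 52.1% and detectable d 0.56.

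**The case against.** The strongest reply is that 160 is not the number that will enter the class comparisons. Attrition is given as an upper limit, maximum likelihood keeps patients with partial data, every patient receives a class, and falls are recorded weekly, so someone who leaves late still contributes a fall rate. This stands as far as it goes: 160 is a floor, and the effective number may be anywhere from 160 to 200. It does not rescue the stated figures, because d = 0.40 has essentially no slack at 200; at 180 both powers are already below 80%. Nor does keeping a patient in the growth model recover the fall follow-up that was lost.

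A second reply is that the plan puts its interpretation of the fall-rate comparison on effect sizes and 95% confidence intervals. That reduces the harm from a misread null result, but it does not make the power statement correct.

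Three stronger readings are tempting, and the document does not support them.

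- *Both d and w need all 200 patients in two equal classes.* For a given w, power depends only on N and df. Class balance does not enter, and 191 suffice at 4 df.
- *The 5% floor contradicts the equal-groups assumption.* Equal groups is a declared assumption, and the floor is a model-selection criterion, not a forecast of class size. Together they show only that the equal-class figure is a best case.
- *Evaluable numbers will be 160.* The text says up to about 20%, and nothing in it treats every withdrawal as non-evaluable.

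**Conclusion.** The point holds in a limited form. The detectable effects for the class comparisons were computed at, or very near, full enrolment, and the attrition allowance in the same paragraph was applied only to the mixture-model rule. With 200 enrolled, 200 evaluable patients and a material loss of up to about 20% cannot both be true.

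The shortfall is moderate: at the floor with equal classes, power is about 9 percentage points under the nominal 80% for d (71.0%) and about 8 under for w at 4 df (71.6%). This rests on the plan's own two-sided 0.05 level, before the Hochberg adjustment planned for the predictor comparisons, on a two-sample t-test for fall rates, and on 160 as the lowest evaluable number. The actual class split is unknown, and any inequality lowers power for d further. The design and analysis are not in question, only the power statement.

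**What to change.** In the sample size section:

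1. State the N behind d and behind w.
2. Replace the claim of evaluable data on 200 with: *200 enrolled, at least about 160 evaluable after up to 20% attrition.*
3. Restate the detectable effects at 160 with equal classes: d about 0.45, and w about 0.27 at 4 df. It may be added that w = 0.25 remains detectable at 1 and 2 df.
4. Label the equal-class d as a best case, because class sizes are an output of the model, and give one unequal example, such as d about 0.56 for a 20/80 split at 160.

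The cost is a few lines of text and slightly less favourable stated figures. Enrolment stays at 200. If the sponsor prefers to keep d = 0.40 after 20% attrition, about 250 would have to be enrolled, but the correction does not require that.
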